Interdepartmental FG^i^	—	—	—	✓	—	✓	—
Nonparticipant observation of MM^j^ session	—	—	—	—	✓	—	—
Individual interviews	—	—	—	—	—	✓	—
Intradepartmental FG	—	—	—	—	—	—	✓

a Not applicable.

b T0: the baseline.

c T1: after the MM information meeting/before the MM test session.

d T2: after the MM test session.

e T3: after the end of the MM program.

f T4: 3 months after the end of the MM program.

g d: days.

h M: months.

i FG: focus group.

j MM: mindfulness meditation.

**Table 2. T2:** Schedule for quantitative evaluations in the PROMIND study.

	Study stage					
	Inclusion-baseline	—^a^	Allocation	—		End of the study
Time point	T0^b^	T1^c^	—	T2^d^	T3^e^	T4^f^
Months	M1-M6^g^	M6	—	M7 ± 15 d^h^	M12 ± 30 d	M15 ± 30 d
Enrollment	✓	—	—	—	—	—
Eligibility screen	✓	—	—	—	—	—
Informed consent	✓	—	—	—	—	—
Allocation	—	—	✓	—	—	—
Quantitative assessments						
Sociodemographic characteristics: questions	✓	—	—	—	—	—
Psychological flourishing in the workplace: EEPMT-13^i^	✓	—	—	—	✓	✓
Mindfulness: FFMQ-15^j^	✓	—	—	—	✓	✓
Hostility/aggression/anger: AQ-12^k^	✓	—	—	—	✓	✓
Impulsivity: VAS^l^	✓	—	—	—	✓	✓
Perceived stress: Chamoux-Simard Scale	✓	—	—	—	✓	✓
Patient support: VAS	✓	—	—	—	✓	✓
Credibility and expectations of MM^m^ intervention: credibility and expectations adapted	✓	✓	—	✓^n^	✓^n^	✓^n^
Occupational stress (working conditions-social support at work): Job Content Questionnaire	✓	—	—	—	✓	✓
Experience of conflict-related disturbance: VAS	✓	—	—	—	✓	✓
Evaluation of collective activity: VAS	✓	—	—	—	✓	✓
Evaluation of organizational leeway: VAS	✓	—	—	—	✓	✓
Psychological safety: VAS	✓	—	—	—	✓	✓
MM practice time (outside MM sessions): questions	✓	—	—	✓^n^	✓	✓

a Not applicable.

b T0: the baseline.

c T1: after the MM information meeting/before the MM test session.

d T2: after the MM test session.

e T3: after the end of the MM program.

f T4: 3 months after the end of the MM program.

g M: months.

h d: days.

i EEPMT-13: Echelle Epanouissement Psychologique Milieu de Travail-13.

j FFMQ-15: Five Facets Mindfulness Questionnaire-15.

k AQ-12: Aggression Questionnaire-12.

l VAS: Visual Analog Scale.

m MM: mindfulness meditation.

n Intervention group (IG) only.

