###### Analysis of the Primary Outcome

For each individual, the psychological flourishing at work was measured (using EEPMT-13) at 2 time points: T0 and T3. Since each individual has 2 measures, and each individual belongs to a given department, we will use a multilevel model for the analysis of the primary outcome [73]. These models, also known as mixed models, are particularly well-suited to the analysis of this type of hierarchical data (ie, first level=the measure, second level=the individual, and third level=the department).

Noting Y_ijk_ as the EEPMT-13 measure j of individual i in department k, we obtain the following model 1 equation:

$$Y_{ijk}=\beta_{0}Z_{k}+u_{ik}+v_{k}+\beta_{1}{\;}^{*}X_{ijk}+\beta_{2}X_{ijk}G_{k}+e_{ijk}$$

where u_ik_, v_k_, and e_ijk_ are, respectively, the individual random effect (individuals having greater or lesser flourishing), the department random effect (certain departments presenting on average greater or lesser levels of flourishing), and the residual deviation of the ijk measure; Z_k_ is a vector of binary indicator variables indicating the department type of department k; G_k_ is an indicator variable for the intervention group (0 if the department belongs to the control group and 1 if the department has received the intervention); X_ijk_ is a measurement time indicator variable (0 if the measurement is taken at T0 and 1 if it is carried out at T3).

With this coding, the 4 fixed parameters making up the β_0_ vector provide mean levels according to the department type (which is a stratification factor in randomization), the parameter β_1_ corresponds to the variation between T0 and T3 for departments belonging to the control group, and β_1_ + β_2_ corresponds to the variation between T0 and T3 for departments belonging to the intervention group. The parameter β_2_ thus corresponds to the parameter of interest that describes the effect of the intervention, and the main hypotheses tested will be as follows:

H0: evolution between T0 and T3 is identical between the 2 groups (ie, β_2_=0)

H1: evolution between T0 and T3 is not identical between the 2 groups (ie, β_2_≠0)

This test will be performed using the Wald test (2-tailed test, type I error rate=5%).

It will be investigated whether a residual effect of the intervention persists at T4, by analyzing the 2 measurements at T0 and T4 in a model similar to model 1.

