###### Missing Data and Software

Every effort was made to minimize the number of missing data. If there are still missing data points, these will be replaced at T0 by the mean of the available data in each group (intervention or control group).

Statistical analysis will be carried out using R software (version 4.5.3; R Foundation for Statistical Computing)) [74].

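### The T4 persistence analysis leaves out the T3 measurement, which can bias the T4 group contrast if T3-related loss to T4 differs between arms

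*Protocol article*

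**What the plan says.** Under Analysis of the Primary Outcome, the protocol article fits model 1 to two measurements per person: "psychological flourishing at work was measured (using EEPMT-13) at 2 time points: T0 and T3". The fixed effects are department type, time and time by group, with random intercepts for person and department. There is no group main effect, so baseline is common to the arms within department type. The time-by-group coefficient β2 "corresponds to the parameter of interest that describes the effect of the intervention".

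For follow-up the section says: "It will be investigated whether a residual effect of the intervention persists at T4". This is to be done "by analyzing the 2 measurements at T0 and T4 in a model similar to model 1".

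The row "Psychological flourishing in the workplace: EEPMT-13" in Table 2 is ticked at T0, T3 and T4 and carries no mark restricting it to the intervention group. So T3 is available in both arms but does not enter the T4 analysis, and no model holds all three times. The only replacement rule under Missing Data and Software is for missing values at T0.

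**The concern.** A likelihood-based mixed model copes with missing outcomes when the loss depends only on what the model contains. In the T0/T4 model that is the T0 score, arm and department type. The T3 score is the measurement nearest to T4 and a natural candidate to explain who answers three months later. If it does explain this, loss that would be ignorable in a model with T3 becomes informative once T3 is removed.

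Differential loss is plausible here. The trial is open-label, only one arm receives the program, and the Limitations section names staff availability as a major difficulty. At stake is the statement about durability. If poor responders in the intervention arm drop out selectively before T4, the effect will look more lasting than it is.

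A second, smaller point concerns the contrast of effects. Subtracting the two β2 values gives a point estimate of how the effect changed from T3 to T4. The two models do not supply the covariance between those estimates, so the change has no confidence interval.

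**Working it through.** **Inputs from the article.** T4 model on T0 and T4 only; EEPMT-13 collected at T0, T3 and T4; 8 × 15 = 120 planned and 108 enrolled. The article gives no effect size, SD, correlation or loss rate, so there is no figure of its own to reproduce on this point.

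**Assumptions, none from the article.** Scores have SD 1. The true effect is 0.4 SD at T3 and 0.3 SD at T4. Where loss to T4 depends on T3, it is logistic with slope -1 per SD. T3 itself is always observed, and department effects are ignored. Correlation set A has all three correlations at 0.6. Set B has 0.5 with T0 and 0.7 between T3 and T4.

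**Formula.** Let δ be the amount by which the T3 mean among T4 returners exceeds the T3 mean of the whole arm. In returners the T4 mean shifts by r34·δ and the T0 mean by r03·δ. Adjusting for T0 removes about r04·r03·δ. Hence

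bias in the T4 contrast ≈ (r34 − r03·r04) × (δ intervention − δ control).

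The multiplier is 0.6 − 0.36 = 0.24 in set A and 0.7 − 0.25 = 0.45 in set B. Numerical integration gives δ in the intervention arm as 0.179 at 21% loss, 0.213 at 25% and 0.253 at 30%. In the control arm it is 0.091 at 10% loss and 0.228 at 27%.

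**Results.** Values in brackets come from large-sample maximum likelihood fits of the T0/T4 model.

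| Loss to T4 | Set A | Set B |
|---|---|---|
| Unrelated to T3 | 0 (0.00) | 0 (0.00) |
| Same mechanism in both arms (27% control, 21% intervention) | 0.24 × (0.179 − 0.228) = −0.012 (−0.012) | 0.45 × (−0.049) = −0.022 (−0.022) |
| T3-related in intervention arm only, 21% | 0.24 × 0.179 = 0.043 (0.041) | 0.45 × 0.179 = 0.081 (0.079) |
| Same, 25% | 0.24 × 0.213 = 0.051 (0.050) | 0.45 × 0.213 = 0.096 (0.096) |
| Same, 30% | 0.24 × 0.253 = 0.061 (0.059) | 0.45 × 0.253 = 0.114 (0.116) |
| Same slope, 10% control and 30% intervention | 0.24 × 0.162 = 0.039 (0.037) | 0.45 × 0.162 = 0.073 (0.079) |

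With all correlations at 0.7 the multiplier is 0.7 − 0.49 = 0.21, and the last row becomes 0.21 × 0.162 = 0.034.

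**With T3 included.** At 21 to 27% loss, the joint T0/T3/T4 model with unstructured covariance had a bias of 0.00 in every scenario and recovered the change in effect (0.3 − 0.4 = −0.10). Adding T3 to a random-intercept model was enough in set A. In set B it left +0.027 when loss was T3-related in the intervention arm only, and +0.048 when the dependence ran in opposite directions in the two arms.

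**Precision.** Take 54 per arm, 25% random loss (40.5 observed at T4) and no clustering. Without T3, SE = √[2(1 − r04²)/40.5]. With T3, SE = √{2[(1 − R²)/40.5 + (R² − r04²)/54]}, where R² is for T4 on T0 and T3.
- Set A, R² = 0.45: 0.178 without T3 and 0.175 with it, about 2% lower.
- Set B, R² = 0.52: 0.192 without T3 and 0.184 with it, about 5% lower.

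**The case against.** The T0/T4 model estimates what the article asks, namely whether a group difference in change from baseline remains at T4. No stated objective calls for a T4-minus-T3 contrast on EEPMT-13. This stands: the choice is conventional and contradicts nothing.

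A reader might infer that the T4 effect is biased as planned. The article does not support that. Dependence of loss on T3 is not enough, because the same mechanism in both arms gives only about −0.01 to −0.02 SD. The dependence or the rate must differ by arm, and no loss data are given. Much larger figures can be produced, but only from extreme patterns. One is 0.12 to 0.20 SD if the whole lowest T3 quarter of the intervention arm fails to return. Another is 0.24 SD in set B at 40% loss with opposite dependence in the two arms. Nothing in the article points to either.

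A reader might also infer that change from T3 to T4 is never estimated, or that collected data are wasted. The first is too strong, since a point estimate exists and only its interval is missing. The second has little force, since the SE falls by 2 to 5%.

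The bias is also modest against sampling error: 0.041/0.178 = 0.23 and 0.079/0.192 = 0.41 of a standard error, before clustering. The joint model's zero bias is partly by construction. People missing at both T3 and T4 contribute no T3 information, and loss that depends on the unseen T4 score biases either model. The study is an exploratory pilot. All of this limits the weight of the point without removing it.

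**Conclusion.** The point holds in conditional form. The article fixes a T4 model that omits an available and relevant measurement. If T3-related loss to T4 differs between arms in strength or rate, the T4 contrast is biased by about 0.03 to 0.08 SD in most of the settings checked, and by just over 0.1 SD in the least favourable one (set B, 30% loss, intervention arm only). Against an assumed T4 effect of 0.3 SD, 0.03 to 0.08 is 10 to 27%. If the mechanism is the same in both arms, the bias is negligible.

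These sizes rest on assumed correlations, loss rates and a logistic loss model. The actual return rates at T3 and T4 will show how much the point matters. It is a minor to moderate weakness in an exploratory follow-up analysis, and it gives no reason to alter the primary T0-T3 analysis.

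**What to change.** Leave the prespecified T0-T3 model as the primary analysis. For the T4 question only:

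- Fit one model to T0, T3 and T4 with department type, time as a three-level factor, time-by-group terms at T3 and T4, and the department random effect.
- Use an unstructured within-person covariance in place of the person random intercept. A random intercept alone forces equal correlations and may remove only part of the bias.
- Report the T4 effect and the T4-minus-T3 contrast, each with a confidence interval, and the number returning EEPMT-13 at T3 and T4 by arm.
- Keep the T0/T4 model as a sensitivity analysis.
- State that the joint model was added after data collection ended on June 30, 2025.

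No new data are needed. The cost is four more covariance parameters (3 × 4/2 = 6 instead of 2) with 8 departments and 108 participants, so the convergence of the fit should be checked. Department-by-time random effects are not required for this fix.

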###### Analysis of Secondary Outcomes

Quantitative secondary outcomes (overall score and questionnaire dimensions) will be described for the population, by demographic variable modality and by intervention group, using standard descriptive statistics. These quantitative criteria will be compared between the 2 groups using the Student *t* test or the Wilcoxon-Mann-Whitney test, according to the distribution.

Categorical secondary outcomes will be summarized for the total population, by demographic variable modality and by intervention group, using the following descriptive statistics: frequencies and percentages for each variable level and for missing values. These categorical criteria will be compared between the groups using the Chi-square test or Fisher exact test, according to the distribution.

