### Allocation of the Groups

Randomization was carried out by the biostatistics team after the MM information meeting. Randomization was carried out at the department level and stratified by department type (medicine, geriatrics, anesthesia-intensive care, and intensive care/neonatology) to ensure that each department type was represented in both the intervention group (4 departments) and control group (4 departments). Cluster randomization was chosen to prevent contamination within departments, as professionals work closely together.

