#### Study Outcome Measures

The primary outcome measure was the evolution of psychological flourishing at work (EEPMT-13) at T0 and at T3. It was measured using the adapted and validated French-language scale Psychological Flourishing at Work (EEPMT-8) [9], to which the Professional Life Satisfaction Scale (ÉSVP-5) [60] was added to form a new 13-item Psychological Flourishing at Work Scale (EEPMT-13).

The secondary outcome measures were as follows:

Evaluation of the impact of the MM program between T0, T3, and T4 at (1) the individual level and (2) the department level: at the individual level, mindfulness was measured using the Five Facets Mindfulness Questionnaire (FFMQ-15; 15 items) [61], hostility, aggression, or anger was measured by the Aggression Questionnaire (AQ-12; 12 items) [62]; impulsivity was measured using a Visual Analog Scale (VAS); perceived stress was measured using the Chamoux-Simard Scale (3 questions as a VAS) [63]; the experience of being disturbed by conflict was measured using a VAS; and patient support was measured using a VAS. At the department level (collective level), job strain was measured using the Job Content Questionnaire (26 items) [64]; collective activity was measured using Likert scales (4 items) [65-67]; organizational leeway was measured using Likert scales (4 items) [68]; and psychological safety at work was measured using a VAS.

The evolution of professionals’ representation of MM:

For all participants, it was measured between T0 and T1 using the credibility and expectancy questionnaire (adapted Devilly and Borkovec Credibility/Expectancy Questionnaire; 6 items) [69].For participants in the intervention group, the evolution of MM representation between T1, T2, T3, and T4 was measured using the credibility and expectancy questionnaire (adapted Devilly and Borkovec Credibility/Expectancy Questionnaire; 6 items) [69].

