### Data Analysis

#### Quantitative Analysis

##### Number of Subjects

As this is a pilot study, the number of participating departments (N=8) and the number of professionals studied (15 professionals per department; N=120) were not determined by a power calculation [70] but by the operational constraints of the study, notably the maximum number of subjects recommended by the MM trainer for a group of meditative practice [55,71,72].

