## Results

The PROMIND study was funded in October 2021, and the funding was extended in June 2024. This study was conducted from May 2024 to June 2025. In total, 108 participants were enrolled in the study; data collection ended on June 30, 2025. Data analysis is in progress. After data analysis, the COPR will be asked to discuss the results and prospects for implementing MM based on the study findings. Workers’ representatives will be informed of the results. A dedicated meeting to summarize and discuss the results of PROMIND will be planned with the participants.

We expect the results of this study to be published by the end of 2026. Scientific publications and communications (national and international) will be planned to publicize this trial and its findings in the fields of psychiatry, public health, and occupational health. Recommendations for publication in the field of epidemiology and realist evaluation will be followed.

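### The between-group tests named for the secondary outcomes treat staff as independent although departments were randomised, and they do not say that T0 is used

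*Protocol article*

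**What the plan says.** Under Allocation of the Groups: "Randomization was carried out at the department level and stratified by department type", so that "each department type was represented in both the intervention group (4 departments) and control group (4 departments". The reason given for clusters is contamination among people who work closely together.

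Under Analysis of the Primary Outcome, a three-level model (measure, individual, department) is used, with department type as a fixed effect. Such models are called "particularly well-suited to the analysis of this type of hierarchical data". EEPMT-13 at T4 is to be analysed in a similar model.

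Under Analysis of Secondary Outcomes, the method changes. For quantitative outcomes (overall scores and questionnaire dimensions), "These quantitative criteria will be compared between the 2 groups using the Student" t test or the Wilcoxon-Mann-Whitney test. For categorical outcomes, "These categorical criteria will be compared between the groups using the Chi-square test or Fisher exact test, according to the distribution". The section names no department term, no department type, and no T0 or change value.

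Under Study Outcome Measures, the secondary outcomes are introduced as "Evaluation of the impact of the MM program between T0, T3, and T4", at the individual level and at the department (collective) level. The collective outcomes are job strain, collective activity, organisational leeway and psychological safety.

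**The concern.** The article accepts for one outcome that staff of a department are not independent, then uses tests that assume they are for the other outcomes in the same people. The two-sample tests take their standard error from the spread between individuals, whereas the treatment was assigned to eight units. If departments of the same type differ for reasons other than the programme, that variation is read as treatment effect. The collective outcomes are where this is most plausible, since colleagues there rate a shared environment, though the article offers no figure to show it.

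A second, distinct matter is that the outcomes are defined as an evolution over T0, T3 and T4, while the tests are described only as comparing scores between groups. If T3 or T4 scores are compared alone, baseline information already collected goes unused, and chance imbalance among eight departments stays in the estimate.

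At stake is how the secondary results are read. According to Integration of Findings, exploratory outcomes feed the judgement on feasibility and scaling up.

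**Working it through.** **Inputs.** From Number of Subjects: "the number of participating departments (N=8) and the number of professionals studied (15 professionals per department; N=120) were not determined by a power calculation". This reproduces: 8 × 15 = 120. From Results: "In total, 108 participants were enrolled in the study", hence 108 / 8 = 13.5 per department. The two-sided 5% level is stated for the primary test and assumed here for the secondary tests. No ICC is given, so a range of 0 to 0.15 is assumed. It means the correlation within departments *after* allowing for department type, because variation between types is balanced across arms by the stratification.

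**Formulas.** Design effect DE = 1 + (m − 1) × ICC. The unadjusted standard error is too small by a factor √DE. True two-sided error of the unadjusted test = 2 × [1 − Φ(1.96 / √DE)]. Effective sample size = 108 / DE.

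Worked case, m = 13.5 and ICC = 0.05: DE = 1 + 12.5 × 0.05 = 1.625; √DE = 1.275; 1.96 / 1.275 = 1.54; true error 12.4%.

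| Within-type ICC (assumed) | DE | √DE | Effective N of 108 | True error at nominal 5% |
|---|---|---|---|---|
| 0 | 1.00 | 1.00 | 108 | 5.0% |
| 0.01 | 1.125 | 1.06 | 96 | 6.5% |
| 0.02 | 1.25 | 1.12 | 86 | 8.0% |
| 0.05 | 1.625 | 1.27 | 66 | 12.4% |
| 0.10 | 2.25 | 1.50 | 48 | 19.1% |
| 0.15 | 2.875 | 1.70 | 38 | 24.8% |

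With the planned 15 per department, ICCs of 0.02, 0.05 and 0.10 give 8.3%, 13.3% and 20.6%.

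**Check by simulation** (no true effect, four types with two departments each, 20,000 trials per setting). With 13 per department and no variation between types, the individual-level t test rejected in 7.8%, 12.4% and 19.0% of trials at ICC 0.02, 0.05 and 0.10. The chi-square test, with a 30% event rate and the ICC on the latent scale, rejected in 6.9%, 10.0% and 13.5%. A comparison of department means paired within type stayed between 4.8% and 5.4% in every setting, including 15 per department.

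**What reduces the inflation.**
- If half of a total ICC lies between types, the simulated error with 13 per department is about 8% at a total of 0.05 and about 12% at 0.10.
- If the within-type ICC is zero, there is none: 5.0%, or 4.4% to 4.5% where types differ.
- If change from T0 is tested, stable department differences cancel, and simulated error is 4.5% to 5.3% at ICC 0.05 to 0.10. If departments change differently over time, the same formula applies with the ICC of the change score, and inflation returns.

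**T0, taken separately.** For a T0–T3 correlation r (assumed), the individual-level variance relative to a T3-only comparison is 1 − r² with baseline adjustment and 2(1 − r) for change scores. For r = 0.5, 0.6 and 0.7 this gives 0.75, 0.64 and 0.51 with adjustment, and 1.0, 0.8 and 0.6 for change. At r = 0.6, adjustment is worth 1 / 0.64 = 1.56 times the sample. This holds at individual level only and does not carry over directly to eight departments.

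**The case against.** The strongest reply is that this is a pilot. The article disclaims confirmatory scope, did no power calculation, asks that associations be read with caution, and states no decision rule for the secondary tests. That lowers the consequence. It does not make the p-values valid, and the tests are fixed by name, so this is not a detail left for an analysis plan.

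Several stronger readings are tempting, and the document does not support them.

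- *That the p-values are certainly too small.* This needs a positive within-type ICC, and none is given. Nor does the article show that the ICC is highest for the collective outcomes.
- *That leaving out T0 also makes p-values too small.* It does not. It loses precision and leaves chance imbalance unadjusted; only ignoring departments inflates error.
- *That the before-after objective is definitely abandoned.* The section does not say which quantity is tested. The Abstract speaks of before-after measurements compared between groups, so change scores are a possible reading. What can be said is that the section does not state it. Change scores would still ignore department-specific change.
- *That every secondary result is affected.* EEPMT-13 at T4 has a model like the primary one, credibility at T2 to T4 is measured in the intervention group only, and qualitative outcomes are not tested.

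**Conclusion.** The point holds in a limited form. The named tests do not match the randomisation or the article's own reasoning for the primary outcome. For a comparison of scores at one time point with 13.5 staff per department, true error at a nominal 5% is about 8%, 12% or 19% at within-type ICCs of 0.02, 0.05 or 0.10. These ICCs are assumptions, and the figures are lower, or unchanged from 5%, in the cases listed above. It applies to the quantitative and categorical secondary outcomes that are compared between groups. The silence on T0 is a separate and lesser fault of precision and of fit to the stated objective. The primary analysis is not touched by this point. Data analysis is described as in progress, so the method can still be corrected and the change recorded.

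**What to change.** Replace the tests under Analysis of Secondary Outcomes by one of the following, and state that T0 is used.

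1. A model of the primary type for each quantitative outcome: time, time by group, department type, individual and department random effects, T0 included, and small-sample degrees of freedom for eight clusters. A department intercept alone cancels from the change over time. If departments may change differently, a department-by-time term is also needed, and eight departments support it only weakly.
2. A comparison of department mean changes paired within department type. This has 3 degrees of freedom, with a critical t of 3.18 against 1.98 for the individual-level test at the planned 120. An unpaired comparison of eight means (6 degrees of freedom) would ignore the stratification.
3. For categorical outcomes, or where a mixed model is unstable, the department-level analysis, or cluster-adjusted estimates and intervals without p-values.

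The cost is small in work, since code for the multilevel model is needed for the primary outcome anyway. The real price is wider intervals and fewer nominally significant results, which reflects what eight departments can show. Record the change and its date.
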